**Figure 3 figure3:**
[figure not shown]
Iterative cocreation of Pregnant Faster. SES: socioeconomic status.

This research group has previously experienced difficulty in including women with a vulnerable health status in an interview study [34]. Although we believe that the nature of the intervention *Pregnant Faster* might encourage more women to participate, we consider these previously obtained experiences. Therefore, for this pilot study, we chose to aim for a sample size of 40 participants (10% of the larger planned cohort study), which we deemed sufficient to provide the first insights supporting further development of *Pregnant Faster*.

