#### Outcome Measures

The main objective of this study design is to establish the feasibility of the app *Pregnant Faster* as a nudge that encourages pregnancy preparation by stimulating the uptake of PCC. Feasibility in this study pertains to overall user satisfaction, the number of booked and visited PCC consultations, and the course of practical conduction with regard to the inclusion process, reward allocation, and finalization. The outcome will be assessed in multiple ways: (1) through the number of women who registered for this study, which indicates the effectiveness of the methods used to reach women; (2) the number of women eligible to participate, which indicates the effectiveness of these methods in reaching the target group; (3) the number of participants who were included and the number who actually started the intervention, which may reveal possible barriers between inclusion and conduction; (4) the number of participants completing the intervention, which offers information on how engaging the app is; and (5) the frequency with which certain rewards are chosen that indicates which rewards are deemed the most desirable and motivating. Furthermore, the usability of the app will be assessed using the MAUQ, a validated 18-item questionnaire on user satisfaction, information arrangement, and usefulness based on a 7-point Likert scale (strongly disagree, disagree, somewhat disagree, neither agree nor disagree, somewhat agree, agree, and strongly agree) as presented in Multimedia Appendix 1 [38].

To further investigate how participants have experienced using the app, the first 10 participants will be interviewed in a semistructured manner to explore the answers they give on questions such as how often they opened the app and if this was according to how often they would have liked to open the app. A topic list and additional information on this interview is present in Multimedia Appendix 2. This topic list and participants’ answers will be converted into a questionnaire offered to the remaining 30 participants. To include the first 10 participants in this questionnaire, the first author will fill in the questionnaire based on the participants’ answers in the interview. The MAUQ and the interview or additional questionnaire will be offered 4 weeks after a participant has started the intervention (T1).

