With regard to the study design, the outcomes comprising *Pregnant Faster’s* feasibility allow for practical evaluation, which will form solid stepping stones to further develop the app. The design of the app is such that we aim to continue its development throughout the coming years and possibly explore its use in different target groups, with and without rewards. A possible limitation in the study design pertains to the interviews with the first 10 participants that have been used to develop the additional questionnaire on user experiences. To evaluate the group of 40 women as one, these interviews will be used to fill out the developed questionnaire. It might be more prudent to qualitatively analyze these interviews and view these 10 participants as a separate group. However, as this feasibility study mainly aims to provide holdfasts for further development of *Pregnant Faster*, we believe that this method will suffice.

A potential risk of using *Pregnant Faster* may be that providing rewards can “crowd out” intrinsic motivation to make healthy choices [45,46]. In other words, the healthy behavior that women value and display before the start of the intervention, diminishes or vanishes after the intervention ends, and rewards are no longer provided. For example, if women went to the gym before the intervention, they could maintain this habit and receive rewards for it. This influences the way they view and value this behavior by shifting their focus from health-related rewards, such as strength and fitness, to material rewards. When the intervention ends and going to the gym no longer leads to material rewards, these women might be less inclined to exercise than they were before they participated in the intervention. This is caused by increasing extrinsic motivation for a behavior at the expense of intrinsic motivation.

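### Ten of the 40 additional user-experience questionnaires are to be filled in by the unblinded first author from interviews and pooled with 30 self-completed forms

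*Protocol article*

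**What the plan says.** The rule is set out in the protocol article under Outcome Measures and taken up again in the Discussion.

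- **Interview.** At T1, "the first 10 participants will be interviewed in a semistructured manner".
- **Questionnaire built from it.** "This topic list and participants’ answers will be converted into a questionnaire offered to the remaining 30 participants".
- **Completion for the first 10.** These women do not fill in the resulting form. Instead: "To include the first 10 participants in this questionnaire, the first author will fill in the questionnaire", working from what they said in the interview.
- **Pooling.** The Discussion (Principal Findings) gives the purpose: "To evaluate the group of 40 women as one, these interviews will be used to fill out the developed questionnaire".
- **Acknowledged alternative.** The same paragraph lists this as a possible limitation: "It might be more prudent to qualitatively analyze these interviews and view these 10 participants as a separate group". It then judges the chosen method adequate, because the study mainly serves further development of the app.

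Three other statements bear on the point. The Randomization and Blinding section says that neither participants nor researchers are blinded. The end of Outcome Measures says that the questionnaires ask why women did or did not register for PCC and whether the app changed their lifestyle, and that the analysis is descriptive. The Overview of the cohort study says that participants fill out the MAUQ themselves.

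**The concern.** The pooled table would mix two kinds of record under one heading. Thirty forms are what women ticked themselves. Ten are what one researcher concluded from a conversation. Four features make the two hard to treat as interchangeable:

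1. **Rater.** The article names a single coder, who is unblinded and belongs to the group that says it developed the app.
2. **Mode.** Answers given to a researcher in a semistructured interview need not match those given on a form. The final items are written after the interviews, so an item may lack a clear interview answer; it must then be inferred or left blank.
3. **Circularity.** The answers of these 10 women help to determine the items and are then used to fill them in.
4. **Order.** The coded forms all come from the first 10 entrants. In a pooled table, the effects of rater, mode and enrolment order cannot be separated.

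The content at stake is useful to the programme. The MAUQ is a fixed, validated 18-item usability scale, so the questions on PCC registration and lifestyle change presumably sit in the additional questionnaire. The Conclusions say that barriers to registering for PCC found here will be addressed before the study continues with 400 more inclusions. The affected items therefore inform the next step.

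**Working it through.** **Inputs**

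- Planned total: "we chose to aim for a sample size of 40 participants (10% of the larger planned cohort study" (cohort study protocol, text after Figure 3).
- Interviewed women whose forms the first author completes: 10 (Outcome Measures).
- Women who complete the form themselves: 30 (Outcome Measures).
- Dropout or non-response: no figure is given. The totals below 40 used here are assumptions.
- Coding shift d: no figure is given. It is kept as an unknown.

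**The plan's own figures.** 10 + 30 = 40, and 10% × 400 = 40. Both agree with the stated sample size.

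**Share of author-completed forms.** 10 / 40 = 25% at full recruitment and response. If all 10 interviews take place but fewer women respond in total, the share is 10 / N:

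| N (assumed below 40) | Author-completed share |
|---|---|
| 40 | 25.0% |
| 35 | 28.6% |
| 30 | 33.3% |
| 20 | 50.0% |

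**Effect on a pooled percentage.** Let d be the difference, in percentage points, between the coded result for the 10 and what the same women would have ticked themselves. The pooled percentage is (10 × coded + 30 × self-completed) / 40, so it moves by (10 / 40) × d = 0.25 × d:

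| d (assumed, points) | Movement of pooled percentage (points) |
|---|---|
| 10 | 2.5 |
| 20 | 5 |
| 30 | 7.5 |
| 100 (ceiling) | 25 |

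The sign of d is not known either.

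**What pooling gains in precision.** The plan proposes no confidence intervals, so this only gauges the cost of separation. The 95% half-width at 50% is 1.96 × √(0.25 / n):

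- n = 40: 1.96 × √(0.25 / 40) = 15.5 points
- n = 30: 1.96 × √(0.25 / 30) = 17.9 points

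Leaving out the 10 coded forms costs 2.4 points of half-width.

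**Which outcomes are touched**

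| Outcome | Source according to the article | Author-completed |
|---|---|---|
| MAUQ | Participants (Overview) | 0 of 40 |
| Registrations, eligibility, inclusion and start, completion, reward choices | Counts (Outcome Measures) | None |
| PCC requests and confirmed visits | Registered during the study (Outcome Measures) | None |
| Additional user-experience questionnaire | 30 women, plus the first author for 10 | 10 of 40 |

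**The case against.** The strongest defence is that the authors saw the issue, named it as a limitation, gave the alternative and explained their choice. The study is a descriptive feasibility pilot, and no test, comparison or threshold is attached to this form. The coder works from what the women actually said. The form derives from the same topic list as the interviews, so the core topics should have come up, and some items, such as how often the app was opened, are largely factual. Building closed questions from earlier interviews is also normal practice.

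Much of this stands and limits the point. Disclosure, however, does not separate the two kinds of record in the table. The developmental aim argues for separation rather than against it: 10 interviews reported as interviews serve app development well, and nothing in the article requires 40 records in this table.

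A reader might be tempted to go further, and the documents do not support that:

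- **That a quarter of all evaluation data is scored by the developers.** The 25% applies to one form only. User satisfaction has its own self-completed instrument, the MAUQ, and PCC uptake is a count.
- **That the coding favours the app.** This is plausible for an unblinded member of the developing group, but nothing in the article shows the direction or the size.
- **That the coding cannot be checked.** The article refers to an appendix on the interviews that is not shown. Whether interviews are recorded or coding is verified is unknown. What can be said is that a pooled table would not show the difference.

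**Conclusion.** The point holds for the additional user-experience questionnaire alone. The article states a rule under which 10 of 40 forms (25%) are coded by the unblinded first author, from interviews that also shaped the form, and merged with 30 self-completed ones. It acknowledges the weakness without adopting the option that it calls possibly more prudent.

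The 25% assumes full recruitment and response. That the form holds the PCC reasons and perceived lifestyle change is a reasonable inference from the wording under Outcome Measures, not an explicit statement. Any bias equals 0.25 × d, with both the size and the sign of d unknown. The MAUQ and the count outcomes, and hence the main measures of satisfaction and PCC uptake, do not depend on this. It is an inexpensive improvement that should be made, not a flaw that endangers the study.

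**What to change.** In Outcome Measures and in the limitation paragraph of the Discussion, replace the pooling rule with text to this effect:

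> The main tabulation of the additional questionnaire contains self-completed forms only. The interviews with the first 10 participants are reported qualitatively. If questionnaire forms are also coded from these interviews, they are shown in a separate column labelled as coded by a researcher, and are not added to the self-completed forms.

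Optionally, the 10 women can be asked to complete the finished questionnaire themselves. Those forms should be labelled as completed late and after an interview on the same topics, because recall and priming make them differ from the other 30. This would also add some burden in a group that the team has found hard to include, so it should not be a condition of the fix.

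**Cost.** A wording change and one extra table column. The main table would hold about 30 instead of 40 records, with the small loss of precision shown above. No new data collection is needed.

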#### Sample Size

The aim of this study is to test the feasibility of *Pregnant Faster* and explore the barriers that might be encountered. On the basis of our previous experiences with including the described target group, we are confident that 40 participants will be sufficient to reach our aim.

### Ethics Approval

This study was assessed and approved by the Medical Ethical Committee of the Erasmus University Medical Center, Rotterdam, The Netherlands (MEC-2020-0974). Considering the low risk of this study, composing a Data Safety Monitoring Board was deemed unnecessary.

## Results

### The App Design

The name *Pregnant Faster* serves as a first microlevel nudge to join the study because most women who wish to have a baby often hope to become pregnant quickly. Using the app and its various components, all of which form microlevel nudges, will lead to earning so-called *coins.* Earning coins functions as a microlevel nudge because it stimulates participants to use the app.

Participants log-in with their email address and a password that yields 1 coin per day. The first log-in yields 50 coins to immediately stimulate the participants to engage with the app. After log-in, a dashboard appears, containing five buttons: (1) Earn coins, (2) Overview coins, (3) See a midwife! (4) This study, and (5) Rewards (Figure 4).

Button 1, “Earn coins,” leads to a timeline in which new information appears daily in blogs or tips. Reading these yields 4 to 8 coins depending on the reading time and reading difficulty. Earning coins acts as a microlevel nudge to engage in reading relevant information about how to adequately prepare for pregnancy and ameliorate lifestyle and preconceptional health. Putting pregnancy preparation into the participant’s focus stimulates active thought on this topic, which in turn may lead to increased motivation for pregnancy preparation and healthier choices. In the same timeline, a daily questionnaire appears in which participants can tick off if they have eaten enough fruit and vegetables, exercised, and taken their folic acid supplements. Each ticked-off point yields 2 coins. This questionnaire also acts as a microlevel nudge because it serves as a reminder and motivator, which may lead to performing the behavior that can be ticked off.

**Figure 4 figure4:**
[figure not shown]
Screenshots of the mobile health app Pregnant Faster.

Button 2, “Overview coins,” displays when and how coins have been earned and how many coins have been spent on which products. Having saved or spent a certain number of coins may nudge women to try and earn more coins, leading them back to the timeline in which they learn about properly preparing for pregnancy.

Button 3, “See a midwife!” contains information regarding what PCC entails and for whom it is meant. Here, we try to encourage participants to sign up for a consultation with a midwife in their vicinity and offer an easy way to sign up for a consultation in their neighborhood by filling in their phone number, which yields 25 coins immediately and an additional 75 coins after the visit has been confirmed. Minimizing the effort required to register for a PCC consultation serves as a microlevel nudge by lowering the threshold to engage in PCC.

Button 4, “This study,” contains information about the study itself, the researchers, and where to find additional information and contact details for questions, help, or complaints.

Button 5, “Rewards,” contains a list of rewards accompanied by images that participants can spend their coins on. Participants can choose from a variety of rewards such as folic acid supplements, fruits, nail polish, mascara, ovulation or pregnancy tests, newborn clothing, water bottles, and other healthy or fun rewards that may contribute to preconceptional health.

In our earlier ethical research and interview study [34], it became apparent that adequately respecting participants’ autonomy and preferences is imperative when it comes to increasing motivation for certain behaviors. Women wanted to have the option to either save up for a large reward or spend their coins on multiple smaller rewards. When participants choose their rewards freely, this will automatically lead them to choose the timing and type of reward that motivates them the most. In other words, being able to freely choose supports the app in stimulating women with different preferences regarding the timing and types of rewards to engage in pregnancy preparation and visit a PCC consultation. To satisfy this requirement, the app contains multiple types of rewards of varying value.

Another microlevel nudge lies in the varying value of the coins. One coin represents a monetary value of €0.06 to €0.26 (US $0.06 to US $0.26). By making healthy rewards, such as folic acid supplements and fruits, relatively cheap, we steer participants toward picking healthy products over luxury goods, while still allowing them to choose luxury goods if that is what stimulates them most to earn coins and engage in PCC. For instance, the mascara and folic acid supplements are of equal monetary value and cost €3.00 (US $3.00). However, the folic acid supplements can be ordered for 10 coins whereas ordering the mascara will cost the participant 35 coins.

Participants of our previously conducted interview study [34] mentioned that it might be painful for them if they could only choose pregnancy and baby-related products, in case of not getting pregnant quickly. To take this into account, we have included rewards in the app that are not relatable to pregnancy or babies, such as water bottles, a book voucher, and resistance bands for physical exercise.

The design of *Pregnant Faster* makes the app suitable for all women because it automatically matches participants’ personal preferences and their current level of motivation to prepare for pregnancy and engage in PCC. This is done by allowing participants to freely choose the type and timing of their rewards and by matching their current “Stage of Change,” as described by Prochaska and DiClemente [39].

The transtheoretical model of behavior change by Prochaska and DiClemente [39] describes the different and subsequent stages of changing a certain behavior: precontemplation, contemplation, preparation, action, maintenance, and relapse (Figure 5). Each stage requires a different type of approach [40]. For instance, if a woman has an unhealthy diet and is currently in the precontemplation stage, is not aware of a problem, and is not willing to change, helping her set up a detailed healthy eating plan may lead to her feeling overwhelmed or rejecting the idea that a healthy diet is important, which results in resistance and noncompliance. The first step for this specific woman would be to help her discover why a healthy diet is important to her and which benefits it could possibly yield for her. This will help her acknowledge that her current diet may be problematic and requires a change: the contemplation stage. However, if the woman has been contemplating improving her diet for a while, helping her set up a practical plan may be the exact nudge she needs to help her reach the next stages of change: preparation and action. The choice to use this model was based on the fact that it is widely used and taught in medical education and health care professions, as it provides solid instructions on how best to approach the patient or client to encourage and support them in changing unhealthy behaviors, in addition to the available evidence regarding its effectiveness [41,42] and the amount of experience of the authors in the application of this model.

It is clear that the most effective approach differs by stage and that the current stage of change is very personal. However, we chose not to assess the participants’ current stage of change to minimize what participants could deem *fruitless engagement*—spending time in the app without being rewarded for it, which could diminish interest in the app. Therefore, *Pregnant Faster* was designed to passively match all possible stages, as described by Prochaska and DiClemente [39]. If a participant is currently not preparing for pregnancy and is not interested in doing so (precontemplation), it is still attractive to read the information *Pregnant Faster* offers because of the coins she can earn and spend on rewards to her liking. The blogs and tips in *Pregnant Faster* focus on conveying that healthy choices and PCC may help to have a healthy baby sooner, a goal that many women strive for. This may cause a participant to start contemplating if she too could get pregnant faster by actively preparing for pregnancy and visiting a midwife for PCC. She might even start to plan how she could take action (preparation). If a participant is already preparing for pregnancy by, for instance, eating more vegetables (action or maintenance), reading about the benefits of this behavior in the timeline of the app will act as a stimulant to maintain this behavior or maybe even make a plan to also eat 2 pieces of fruit per day (preparation). For women who already have a healthy diet and lifestyle, and are currently in the maintenance stage, the app will serve as a stimulant to sustain healthy behavior and may help to prevent a relapse (maintenance). In conclusion, the app appeals to women in each stage of change by either encouraging new healthy behavior or the continuation of preexisting healthy behavior.

**Figure 5 figure5:**
[figure not shown]
The transtheoretical model of health behavior change by Prochaska and DiClemente [36]. (1) Precontemplation: unaware of the need for change and unwilling to change. (2) Contemplation: aware of the problem but not yet committed to change. (3) Preparation: believes change is good, intent on taking action, and planning to start. (4) Action: actively changing behavior or creating new habits. (5) Maintenance: behavior has changed, committed, and resolved; must be aware of the possibility of relapse. (6) Relapse: relapsing into old behavior; may skip precontemplation in the next cycle.

Participants in any stage of change may choose to register for a PCC consultation as the reward is high and the required action (filling in their phone number) is relatively small. This was decided consciously to meet the main objective of *Pregnant Faster*, stimulating pregnancy preparation by visiting a PCC consultation provided by a health care provider. These face-to-face consultations allow health care providers to directly apply motivational conversation techniques [43] and actively match the participant’s current stage of change on the topics that are most relevant for them, for instance, smoking cessation, an unhealthy diet, or a sedentary lifestyle. Having an engaging, live conversation in which the participant can ask questions and feels heard and supported may be the greatest encouragement or nudge to engage in adequate pregnancy preparation and make healthy choices. Furthermore, a live consultation allows for relevant referrals (eg, for smoking cessation) without relying on the participant to take the first step.

This intervention is completed after 4 weeks. If women still have coins left by the end of the intervention, they will be able to exchange these for rewards within 2 weeks after the completion date or 2 weeks after their PCC consultation. The app and timeline will continue to be available for participants, so they can access its information and register for a PCC consultation whenever they please, but they will no longer be able to earn or spend coins by using the app.

The iterative developmental process has led to the detailed design of the app *Pregnant Faster*, which we have built in cooperation with the event agency Improve in Delft, the Netherlands, and the mobile app manufacturer TJIP The Platform Engineer. *Pregnant Faster* is an app of 5.2 MB and is currently only available in the research setting for Android by a download link and for iPhone through the Apple store. The app has a modern, colorful interface (Figure 4) inspired by the preferences of the target group. Overall, the app was designed to fit the user’s needs and preferences concerning the content of the app as well as easy and intuitive operating.

